Inclusion criterion number 4 is designed to assure equal access to therapy at study enrollment. ART will not be provided as part of this study. Coverage for ART will be addressed through patients’ primary care clinics. In our study population, antiretroviral therapy coverage is generally obtained through Medicaid or the Maryland AIDS Drug Assistance Program (MADAP). Our site managers will assist individuals in accessing appropriate resources, but participants will not be enrolled until medication coverage and receipt of prescriptions from a medical provider has been verified. Exclusion criterion 3 is designed to exclude individuals with such extensive drug resistance that viral suppression is unlikely, even with high-level adherence. A summary resistance profile will be compiled that assumes that any resistance mutation or phenotypic drug resistance documented in the past is never lost. The cumulative mutation list will be entered into the Stanford University web-based HIV drug resistance database ([http://hivdb.stanford.edu](http://hivdb.stanford.edu/)) for analysis. Drugs in the proposed regimen will be considered to be fully active (i.e., score=1.0) if categorized as “susceptible” or “potential low-level resistance”, and to be partially active (i.e., score=0.5) if categorized as “low-level resistance” by the Stanford database. Drugs in the proposed regimen with “intermediate“ or “high-level” resistance will not be assumed to have any antiviral activity. Results from phenotypic resistance tests (if available) will be incorporated into the assessment individual drug activity. Enfuvirtide (fusion inhibitor) and raltegravir (integrase inhibitor) will be assumed to be fully active if they have not been used previously. CCR-5 inhibitors (e.g., maraviroc) will be assumed to be fully active if an agent in this drug class has not been used previously and a tropism assay performed within the previous 4 weeks shows exclusively R5-tropic virus. Scores form each drug in the proposed regimen will be summed for a “regimen activity score.” To be eligible for the study a participant’s “regimen activity score” must be greater than or equal to 1.5.

Enrollment and randomization

120 participants will be enrolled to assess the outcomes of this study.

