Participants’ HIV medical providers will select the antiretroviral regimens to be used. Bias would be introduced if medical providers selected antiretroviral therapy regimens differently based upon knowledge of whether their patient had been randomized to DAART or to SAT. For example, it is possible that medical providers would be more likely to select an antiretroviral therapy regimen that is dosed once daily in individuals enrolled to DAART. This might lead to significant differences between the groups in the use of specific antiretroviral drugs or combinations that could confound the analysis. To avoid this potential source of bias, each medical provider will be asked to specify the particular antiretroviral regimen that he or she will prescribe prior to participant randomization. Our clinical trial is flexibly designed to assess the efficacy of DAART in patients with a range of clinical characteristics, and antiretroviral needs. The study coordinator will contact the data manager for random treatment assignment. Randomization (1:1; performed with Stata, version 8.0, College Station, TX), stratified by prior antiretroviral exposure (naïve or experienced), and study site (PAODD, New Hope, or Day Break), will be performed in blocks randomly varying sized 2 to 6. Antiretroviral naïve will be defined as having less than 4 weeks exposure to antiretroviral drugs.

DAART arm

Site managers will take verbal orders or receive facsimiles of prescriptions from participating medical providers. The site managers will transcribe the medication information to standardized pharmacy order forms, which specify how medications are to be packaged together. We have established a relationship with a single pharmacy, Johns Hopkins Pharmaquip, which will be used for all sites except the VA. Since veterans receive medications free of charge through the VA system, medications for this study will be prepared and packaged at the VA pharmacy. In accordance with pharmacy practice and guidelines, a licensed pharmacist will prepackage all doses of therapy in re-sealable plastic bags. Four-week supplies of therapy will be pre-packaged and will be delivered to the methadone clinics. Pre-packaged therapy will be stored in locked cabinets at each site. Participants will be given a 3-day “emergency supply” of their therapy to permit continued therapy on unplanned absences from the OTP. The site managers will replenish emergency supplies as needed.

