| Change in HIV RNA (log10) from baseline | Continuous: compare in DAART and SAT at 4 time points (3, 6, 12, and 18 months) | Intent-to-treat, missing values excluded | ANOVA for each time point and linear regression with GEE for overall comparison |
| **CD4 cell recovery** | | | |
| Change in CD4 cell count from baseline | Continuous: compare in DAART and SAT during active intervention (3, 6, and 12 months) | Intent-to-treat | ANOVA for each time point and linear regression with GEE for overall comparison |
| CD4 cell count | Continuous | Intent-to-treat | Linear regression with GEE & adjusting for initial CD4 at baseline |
| **Antiretroviral therapy use** | | | |
| Retention to ART | Time to failure: first day of ART cessation lasting ≥ 14 days, self-report | Intent-to-treat | Kaplan-Meier curves and Log-rank test |
| Cumulative ART use time | Continuous: number of weeks ART used in 12 months, self-report | Intent-to-treat | Wilcoxon rank-sum test |
| **Development of drug resistance** | | | |
| Antiretroviral drug resistance | Binary: presence of IAS-defined drug resistance mutations (during 12-month intervention phase) that were not present in baseline sample or in resistance test conducted prior to study (if available) | Intent-to-treat, missing values excluded | Chi-square test |
| **Substance abuse treatment outcomes** | | | |
| Retention to substance abuse treatment | Time to failure: discontinuation from opioid-treatment program | Intent-to-treat | Kaplan-Meier with log-rank test; Cox proportional hazards model adjusting for prior time in methadone program |
| Active drug use | Continuous: proportion of total available drug screens positive for opiates or cocaine. [Protocol-driven and clinical drug screens (required monthly by law in methadone clinics)] | Intent-to-treat, missing excluded, censored at methadone discontinuation | Wilcoxon rank-sum; Poisson regression with count of positive screens per follow-up months excluding periods with no testing |

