We will carry out a primary unadjusted analysis comparing study endpoints in the DAART and SAT arms. Two-sided P values < 0.05 will be considered to be statistically significant. The primary endpoint for this study will be suppression of the viral load below 50 c/ml evaluated at the 3 follow-up visits during the active intervention period (3, 6 and 12 months). Statistical generalized linear models for repeated observations will be used with the generalized estimating equations (GEE) approach to account for intra-person correlation. An intent-to-treat rule will be used, with missing values excluded. An 18-month follow-up (6 months after DAART intervention concludes) will be performed as a secondary analysis to assess durability. A supplementary on-treatment analysis will also be conducted. Secondary, multivariate analyses will be used to adjust for differences in possible confounding variables that may arise despite randomization. Data collection for the study will include detailed demographic, clinical, and psychosocial factors that may be associated with study outcomes, including prior opportunistic conditions, hepatitis B and C, baseline CD4 count and HIV RNA level, prior treatment experience, and validated metrics of drug and alcohol abuse, depression, and quality of life. We will assess whether adjustment for potential confounders, using multivariate modelling techniques, affects study inferences.For the analysis of immune restoration, we will use an intention-to-treat approach, with last observation carried forward for missing data points. The mean change in CD4+ cell count from baseline will be compared in the study arms at the designated follow-up times. Alternatively, a survival analysis approach will be used with time until first CD4 increase >100 or counts >500 as the outcome and censoring at last visit for each person.

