**Statistical power**

In this analysis, we will use methods that can incorporate repeated measurements and account for possible intra-person correlations. Such methods include generalized linear models with generalized estimating equation (GEE) approach or random effects models that can handle binary as well as continuous outcomes. Thus, overall, the number of observations available for comparison of the experimental and control arms of the study will be increased and missing observations will be excluded only for the time points where values of the outcome are missing. Calculations of sample sizes are based on models for longitudinal data analysis (Diggle PJ, Heagerty P, Liang KY, Zeger SL. Analysis of Longitudinal Data. 2002 Oxford University Press, Publ.) are shown in the following table.

The table below shows the power to detect a range of deltas in the DAART arm according to different viral suppression rates in the SAT arm, assuming alpha=0.05, enrollment of 60 per study arm, an intra-subject correlation of 0.2, and 15% loss to follow-up over one year. The table demonstrates >80% to detect deltas >0.20 across varying assumptions.

| **Table. Study Power with sample size of 60 per arm.** | | | | |
| --- | --- | --- | --- | --- |
| **Proportion in control (P0)** | **Delta in DAART arm (P1-P0)** | | | |
|  | **0.15** | **0.18** | **0.20** | **0.25** |
| 0.25 | 0.659 | 0.804 | **0.875** | **0.969** |
| 0.30 | 0.628 | 0.778 | **0.854** | **0.962** |
| 0.35 | 0.609 | 0.762 | **0.842** | **0.958** |
| 0.40 | 0.599 | 0.756 | **0.838** | **0.958** |

|  |  | | |
| --- | --- | --- | --- |
|  |  |  |
|  |  |  |  |
|  |  |  |  |
|  |  |  |  |
|  |  |  |  |
|  |  |  |  |
|  |  |  |  |
|  |  |  |  |
|  |  |  |  |
|  |  |  |  |
|  |  |  |  |

Differences of 15% to 20% in viral suppression rates are frequently considered to be evidence of therapeutic superiority in clinical trials comparing antiretroviral regimens. The detectable difference afforded by our sample size is conservative compared to the differences that we estimated in our pilot study. At 6 months and 12 months the absolute differences in viral suppression between DAART and the methadone maintained group who were self-administering HAART were +30 and +23, respectively.

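### Continuous HIV RNA is compared only as an unadjusted change score, and CD4 leads with one although a baseline-adjusted model is already listed; adjusting would give modest extra precision on these secondary outcomes at no cost

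*Protocol*

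**What the plan says.** Three places in the protocol's Study Statistics section bear on this.

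- **Secondary outcomes table, HIV RNA.** Change from baseline in log10 HIV RNA is compared at 3, 6, 12 and 18 months by "ANOVA for each time point and linear regression with GEE for overall comparison". No baseline covariate is named. The other HIV RNA rows are binary (below 50 or 400 c/ml).
- **Secondary outcomes table, CD4.** There are two rows. Change in CD4 uses the same ANOVA and GEE wording. CD4 count as a level uses "Linear regression with GEE & adjusting for initial CD4 at baseline". The table does not say which leads.
- **Statistical plan.** The primary comparison of study endpoints is to be unadjusted. For immune restoration the text says: "The mean change in CD4+ cell count from baseline will be compared in the study arms at the designated follow-up times". It carries the last observation forward, offers a time-to-event analysis as an alternative, and does not mention the adjusted row. Separately, secondary multivariable analyses are planned to deal with confounders that arise despite randomisation. Baseline CD4 and HIV RNA appear in the list of factors collected for that purpose.

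HIV RNA and CD4 are both scheduled at month 0 (Study Design diagram), so the covariates will exist.

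**The concern.** Subtracting the baseline is not the same as adjusting for it. A change-score comparison forces the slope of follow-up on baseline to be 1. If the true slope is smaller, baseline variation that adjustment would remove stays in the arm comparison.

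HIV RNA shows this clearly because suppression puts a floor under the follow-up value. Take two participants suppressed at 50 c/ml, which is 1.70 log10. One entered just above the eligibility limit of 500 c/ml (2.70 log10) and the other at 50,000 c/ml (4.70 log10). Their changes are about -1.00 and -3.00, yet their outcome is the same. Among suppressed participants the change score is essentially the baseline with its sign reversed.

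What is at stake is precision on two secondary outcomes in a trial of about 60 per arm. For CD4 there is also the question of which listed analysis carries the conclusion.

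**Working it through.** **1. The plan's own figure.** The only power figures are for the binary primary endpoint, "assuming alpha=0.05, enrollment of 60 per study arm, an intra-subject correlation of 0.2, and 15% loss to follow-up over one year". The test level is stated as: "Two-sided P values < 0.05 will be considered to be statistically significant". Endpoint visits are those "evaluated at the 3 follow-up visits during the active intervention period (3, 6 and 12 months".

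- Retained per arm: 60 x 0.85 = 51.
- Effective n per arm: 51 x 3 / (1 + 2 x 0.2) = 109.3.
- A pooled two-sided test of two proportions at a control rate of 0.25 then gives power 0.660, 0.806, 0.878 and 0.973. The table has 0.659, 0.804, 0.875 and 0.969.
- All 16 cells agree within 0.0075.

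The table therefore reproduces, and nothing below touches it. The 0.2 is a within-person correlation for the binary endpoint and cannot serve as a baseline-to-follow-up correlation for log10 HIV RNA or CD4.

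**2. General formula, one visit.** Let r be the baseline-to-follow-up correlation and k the follow-up SD divided by the baseline SD. In units of the baseline variance:

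- change score: k² + 1 - 2rk
- baseline-adjusted: k²(1 - r²)
- difference: (1 - rk)²

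The difference is never negative, and it is zero only when the slope rk equals 1. So in large samples adjustment cannot lose, but it may gain nothing (for example k = 2, r = 0.5).

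**3. Equal SDs (k = 1).** The ratio of adjusted to change-score variance is (1 + r)/2.

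| r (assumed) | ratio | variance saved |
|---|---|---|
| 0.2 | 0.60 | 40% |
| 0.5 | 0.75 | 25% |
| 0.7 | 0.85 | 15% |
| 0.9 | 0.95 | 5% |

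This illustrates the principle. Equal SDs are a poor description of HIV RNA with a floor, so the table should not be read as the size for that outcome.

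**4. HIV RNA with a floor at 50 c/ml.** Assumed inputs: 51 per arm, baseline mean 4.5 and SD 0.8 log10.

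- One set of simulations (4,000 trials per scenario) gave standard errors, change score against adjusted, of 0.233 v 0.224, 0.229 v 0.223 and 0.228 v 0.216. The variance reductions are 1 - (0.224/0.233)² = 7.6%, 1 - (0.223/0.229)² = 5.2% and 1 - (0.216/0.228)² = 10.2%.
- A second set truncated baselines at 500 c/ml, took suppression of 45% v 25% or 60% v 40%, and a correlation of 0.3 to 0.7 among the unsuppressed. It gave 11% to 21%.

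Together the range is roughly 5% to 21%.

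**5. What that range means.** If the change score had 80% power at 51 per arm, its standardised effect would be 1.96 + 0.84 = 2.80.

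- Variance lower by 5%: 2.80/√0.95 = 2.87, power about 82%. The change score would need 51/0.95 = 54 per arm to match.
- Variance lower by 21%: 2.80/√0.79 = 3.15, power about 88%. The change score would need 51/0.79 = 65 per arm to match.

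**6. Chance imbalance.** With 60 per arm and SD 0.8, the 95% range of the baseline difference is ±1.96 x 0.8 x √(2/60) = ±0.29 log10. The share that enters the change-score contrast is 1 minus the slope. If a pooled proportion p is suppressed regardless of baseline, and the unsuppressed have the baseline SD, the slope is (1 - p)r. With p = 0.35 and r = 0.7 the share is 1 - 0.455 = 0.55. With p = 0.50 and r = 0.3 it is 1 - 0.15 = 0.85. The second set of simulations gave 54% to 86%, against about 0% to 3% after adjustment.

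**The case against.** **Adjustment is already planned.** The statistical plan promises secondary multivariable analyses, lists baseline HIV RNA and CD4 among the factors collected, and will check whether adjustment alters the inferences. This stands in part: the protocol does not ignore baseline. But it is a check for confounding placed after the unadjusted result, and it does not specify the model for the continuous outcome.

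**CD4 is already covered.** A reader might infer that CD4 has no adjusted analysis, or that it has two rival adjusted ones. Neither is so. There is one adjusted GEE beside one unadjusted change score. For CD4 the fault is only that the text leads with the less precise analysis.

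**The order is a legitimate choice.** The plan does put unadjusted analyses first in general, so this is not a contradiction. It remains an inefficient order for continuous outcomes whose baselines are in hand.

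**Chance imbalance is not bias.** A reader might take the ±0.29 log10 as an error on top of the reported one. It is not. Under randomisation the change score is unbiased and its standard error already contains that variation. The cost is precision only. The Study Design diagram also lists HIV RNA as a stratifier, while the Study Summary and the randomisation text do not. If it was used, imbalance would be smaller, and that would be a further reason to include it in the model.

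**The size is uncertain.** This stands. A reader might carry over the equal-SD result that, at r = 0.6, the change score needs about 25% more participants (1/0.80 = 1.25). That rests on an assumed equal variance and correlation that do not suit HIV RNA. On the first set of simulations the standard error falls by only about 3% to 5%.

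**Conclusion.** The point holds as one of efficiency. The protocol fixes an unadjusted change-score comparison for log10 HIV RNA, has no baseline-adjusted row for it, and for CD4 gives the unadjusted change the lead in the text although a baseline-adjusted GEE is listed.

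For HIV RNA the avoidable variance is roughly 5% to 21%, conditional on an assumed baseline mean of 4.5, SD of 0.8 log10, a floor at 50 c/ml and 51 per arm. It may be near zero where the slope on baseline is near 1. For CD4 no figure can be fixed from the protocol, and the adjusted model is already there.

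No bias and no inflated error rate is shown. These are secondary outcomes. The binary primary endpoint, its power table and the sample size are unaffected.

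**What to change.** In the secondary outcomes table and the statistical plan text:

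- **HIV RNA:** make the lead analysis a linear GEE on follow-up log10 HIV RNA with arm, visit and baseline log10 HIV RNA. Take the per-visit contrasts from that model in place of separate ANOVAs on change.
- **CD4:** name the baseline-adjusted GEE already in the table as the lead analysis, and align the immune restoration paragraph with it.
- **Both:** keep the unadjusted change-score comparisons as supportive.

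The cost is wording only. Both baselines are scheduled for every participant, and no visit, assay or sample size changes.

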Subjects allocated to the SAT arm will self-administer antiretroviral therapy. Participants assigned to SAT will receive a level of support commensurate with standard clinical practice. Participants in SAT will not be precluded from participating in any adherence-promoting resources available in their clinic or the community. It is important to acknowledge that the DAART intervention is multifaceted, and its effects on adherence and treatment outcomes may be mediated through several mechanisms. Similarities and differences between DAART and SAT are shown in the Table below**.**

| Table. Comparison of interventional factors in DAART and SAT | | |
| --- | --- | --- |
| Factors | **DAART** | **SAT** |
| Medical follow-up by regular medical provider |  |  |
| ART chosen by medical provider prior to randomization |  |  |
| Proof of coverage for prescription medications prior to enrollment (access to therapy) |  |  |
| Access to adherence aids, interventions, or programs available through medical clinics or community resources (excluding other supervised therapy programs) |  |  |
| Study laboratory test results forwarded to medical providers to assist in patient management |  |  |
| Ingestion of ART supervised at OTP on weekday mornings |  | No |
| Non-observed ART doses pre-packaged in re-sealable plastic bags |  | No |
| Medication supplies monitored and refills obtained for participants by site managers |  | No |
| Frequent contact with site managers - opportunity for dialogue/encouragement |  | No |
| Facilitated communication with participants’ medical providers |  | No |
| Medications for other medical and psychiatric conditions directly administered | No | No |

Participant follow-up tracking

In the proposed study we will obtain detailed contact information from participants, including current address, phone number, work number, cell phone number, and pager number. Additionally, we will ask participants to identify and provide contact information for two individuals with whom they have had longstanding relationships (such as family members). Prior to assessment visits, participants who remain in the OTPs will be given verbal reminders and a written reminder of their upcoming visit. Attempts will be made to locate study participants who are no longer attending the methadone clinic through reminder letters, telephone calls, and personal contacts.

Data collection timeline

| **Assessment/Procedure** | **Time (months)** | | | | | | |

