The development of new antiretroviral drug resistance will be compared in the DAART and SAT arms. Genotypic antiretroviral resistance testing will be performed on the last available plasma sample from (3, 6, 12, or 18 months) when the HIV RNA > 500 c/ml and the subject remains on antiretroviral therapy. Stored plasma from baseline will be run simultaneously to determine if new resistance mutations have developed. Antiretroviral resistance testing is generally not possible at viral loads below 500 c/ml to 1,000 c/ml. Drug resistance mutations will be interpreted according to the classification system of the International AIDS Society – USA [3]. Development of antiretroviral resistance will be defined as the presence of  1 major resistance mutation in the protease or reverse transcriptase genes during study follow-up that was not present at baseline. Subjects with HIV RNA levels < 500 c/ml at all follow-up time points will be considered to have not developed drug resistance. Participants who are lost to follow-up, or who have HIV RNA levels > 500 c/ml, but in whom genotypic antiretroviral resistance testing is not technically feasible, will be omitted from the analysis. Exploratory analyses are planned on treatment-naïve and –experienced subgroups, and on differences in the development of protease inhibitor-, non-nucleoside reverse transcriptase inhibitor-, and nucleoside reverse transcriptase inhibitor-associated resistance mutations.

Retention to opiate agonist therapy will be compared in the DAART and SAT arms using survival analysis techniques. Follow-up time will be modeled from the date participants initiated opiate agonist therapy (origin), with subjects coming under observation at study enrollment, to account for delayed entry and potential lead time bias. Subjects will be considered to have failed when they discontinue or are discharged from methadone maintenance therapy. We will also compare the proportion of participants with active substance abuse at baseline and during the study in the DAART and SAT groups. Active substance abuse will be defined as having a urine toxicology screen positive for drugs of abuse or self-reported (ACASI) illicit drug use, or at-risk alcohol use in the 3 months preceding the survey assessment. Logistic regression with generalized estimating equations, will be used to compare the longitudinal risk of active substance abuse in the study groups, with standard errors adjusted for repeated observations.

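### The active-drug-use comparison is labelled intent-to-treat but is censored at leaving methadone, which the same table compares between arms; it is a while-in-programme contrast and can be biased

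*Protocol*

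**What the plan says.** The relevant text is in the protocol's Study Statistics section and in Participant follow-up tracking.

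- **Active drug use, outcome** (secondary outcome table): "Continuous: proportion of total available drug screens positive for opiates or cocaine". Clinic screens and study-visit screens are pooled.
- **Active drug use, approach:** "Intent-to-treat, missing excluded, censored at methadone discontinuation".
- **Active drug use, methods:** "Wilcoxon rank-sum; Poisson regression with count of positive screens per follow-up months excluding periods with no testing".
- **Retention in substance abuse treatment, the row above:** "Time to failure: discontinuation from opioid-treatment program", compared between arms. The statistical plan text repeats the definition: "Subjects will be considered to have failed when they discontinue or are discharged from methadone maintenance therapy".
- **A second drug-use analysis** (statistical plan text): a composite of positive urine, self-reported illicit use and at-risk drinking. For it, logistic GEE "will be used to compare the longitudinal risk of active substance abuse in the study groups, with standard errors adjusted for repeated observations". No censoring at discontinuation is stated.
- **People who leave:** "Attempts will be made to locate study participants who are no longer attending the methadone clinic". The Study Summary schedules urine at every assessment visit (baseline, 3, 6, 12 and 18 months).

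**The concern.** The protocol treats staying in the programme as something DAART may change, and the DAART arm section ends DAART when a participant leaves. Cutting off drug-use data at that point selects on a consequence of randomisation. What remains answers a narrower question: how often screens are positive while people are still enrolled. Study-visit urine obtained from traced leavers would be discarded.

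Suppose DAART keeps more active users enrolled. The censored comparison could then hide a benefit, or show an apparent harm, and the intent-to-treat label would lead a reader to trust it as a randomised contrast.

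Two smaller points concern the Poisson model. Its denominator does not match the outcome defined in its own row, and the row names no allowance for repeated screens on the same person.

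**Working it through.** The protocol gives no power, error rate or expected positivity for this outcome, so there is no figure to reproduce. What follows is illustration under stated assumptions.

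**1. Censoring: what is cut off**

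Input from the protocol: the site table gives 12-month methadone retention of 70% to 90%. Assumptions: the two ends serve as arm values (SAT 70%, DAART 90%); leaving times are exponential; positivity is 40% in programme in both arms and 60% or 80% after leaving.

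Share of the first 12 months spent in programme = (1 − r) / (−ln r).

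- r = 0.70: 0.30 / 0.3567 = 0.841
- r = 0.90: 0.10 / 0.1054 = 0.949

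So about 5% to 16% of person-time is cut. Full-period positivity = share in × 0.40 + share out × positivity after leaving.

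| Positivity after leaving | SAT | DAART | Full-period difference | Censored difference |
|---|---|---|---|---|
| 60% | 0.841×0.4 + 0.159×0.6 = 0.432 | 0.949×0.4 + 0.051×0.6 = 0.410 | −2.2 points (ratio 0.95) | 0 |
| 80% | 0.841×0.4 + 0.159×0.8 = 0.464 | 0.949×0.4 + 0.051×0.8 = 0.420 | −4.3 points (ratio 0.91) | 0 |

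At 75% against 85% retention the differences are 1.1 and 2.2 points. At 80% in both arms they are 0. If positivity does not change on leaving they are 0 at any retention.

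**2. Censoring: heavier users leave sooner**

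A simulation used 60 per arm, monthly screens, mean positivity 40%, within-person correlation 0.4 and no true arm effect. With nominal retention of 70% against 90%, and a log-hazard of leaving that rises by an assumed 3 to 5 per unit of a person's positive rate, the pooled Poisson rate ratio (DAART to SAT) moves to 1.10 to 1.19, a spurious harm. With no link between use and leaving it is 1.00; with the link but equal retention it is 1.01. Wilcoxon rejection stayed at 0.050 to 0.052 here, because each person's own positivity was held constant. The Wilcoxon test is exposed by the mechanism in step 1, where use changes after leaving.

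**3. Poisson denominator**

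Take 40% positivity and one clinic screen a month. Twelve clinic screens give 12 × 0.4 / 12 = 0.40 positives per month. Adding the urine at months 3, 6 and 12 makes 15 screens and 15 × 0.4 / 12 = 0.50 per month. Positivity is the same, yet the rate is 1.25 times higher. That is the extreme between two people; a between-arm shift would need study-visit attendance to differ by arm and would be smaller.

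**4. Poisson variance, if left model-based**

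For T yes/no screens with positivity p and within-person correlation ρ, true variance over Poisson variance = (1 − p)(1 + (T − 1)ρ). Type I error is the two-sided normal tail beyond 1.96 divided by the square root of that ratio. With T = 12 and p = 0.4:

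- ρ = 0: ratio 0.60, type I error 0.011 (conservative)
- ρ = 0.2: ratio 0.6 × 3.2 = 1.92, type I error 0.157 (simulated 0.149)
- ρ = 0.4: ratio 0.6 × 5.4 = 3.24, type I error 0.276 (simulated 0.273)

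At ρ = 0.2 the error is 0.221 for p = 0.2 and 0.083 for p = 0.6. Break-even ρ = p / [(1 − p)(T − 1)] = 0.4 / 6.6 = 0.06. Simulated type I error with person-level robust variance was 0.047 to 0.053 for ρ from 0.1 to 0.6. The Wilcoxon test held at 0.044 to 0.058 in all null scenarios.

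**The case against.** Several objections stand and limit the point.

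- **Bias is not demonstrated.** A reader might infer that the estimate is wrong as a matter of fact. The documents do not show that: bias needs retention to differ by arm and leaving to be related to use, and the protocol gives evidence of neither. The 70% and 90% belong to two different clinics. Randomisation is stratified by site, so the spread between clinics says nothing about a spread between arms.
- **A larger size is tempting.** Counting every leaver as out of programme all year gives 0.70×0.4 + 0.30×0.8 = 52% against 0.90×0.4 + 0.10×0.8 = 44%, or 8 points. That describes month 12 only. Since leaving is spread over the year, the same assumptions give 4.3 points.
- **The Poisson variance is not specified.** A reader might infer naive standard errors. The row says only Poisson regression; a dispersion term or robust variance may properly sit in the analysis plan, which is not shown. The correlation of 0.2 appears in the protocol for viral suppression, not for urine screens.
- **Wilcoxon is listed first.** It uses one proportion per person, with screens as denominator, so neither Poisson complaint touches it. It does share the censoring.
- **The composite GEE covers part of the ground.** It has adjusted standard errors and no stated censoring, but its outcome is broader, and the protocol does not say which of the two drug-use comparisons governs.
- **The cut-off has a rationale.** Clinic screens exist only during enrolment, and later urine depends on tracing, so it may itself be selectively missing.

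None of this removes the conflict between the label and the censoring rule, both of which are written in the protocol.

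**Conclusion.** The point holds in limited form. As written, the active-drug-use row is a while-in-programme analysis carrying an intent-to-treat label, and it sets aside scheduled urine from people who have left. This applies to both listed tests. Under the assumed positivity and retention, the distortion is about 2 to 4 percentage points, and it is zero with equal retention; the actual size cannot be derived from the documents.

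The Poisson denominator does not match the defined outcome. The variance problem is conditional: it arises only if the variance is model-based and the within-person correlation exceeds a low threshold (about 0.06 at 40% positivity and 12 screens). Below that threshold the test is conservative. One secondary outcome is affected, and the primary viral-load endpoint is not.

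**What to change.** Make the intent-to-treat drug-use comparison a logistic GEE with robust standard errors on study-visit urine (opiates or cocaine), using every sample obtained regardless of programme status. This is the method the protocol already uses for its composite.

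Keep the pooled clinic and study-visit analysis, censored at discontinuation, as supportive. Relabel it while-in-programme and present it beside the retention result. In that analysis, replace positives per month with positives out of screens done (number of screens as denominator or offset), and state a person-level robust variance.

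The cost is analysis wording only, because the urine is already scheduled. There are two downsides. Each person contributes fewer screens to the main comparison: at most three in the 12-month intervention period and a fourth at month 18. Screens after discontinuation also depend on successful tracing, so the number expected and obtained should be reported by arm and by programme status.
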